**Figure 6: Aim 1**

[figure not shown]

consequence of treatment assignment. We will model outcomes with logistic (e.g., onset analyses), continuous, Poisson, or Negative Binomial distributions as appropriate. Ancillary analyses will examine intervention effects on marijuana and nicotine use. We also will consider group differences in alcohol use trajectories using latent growth curve models that permit evaluation of differences in the rates of change (including nonlinear trajectories) in alcohol use. We have used these techniques extensively in past research.

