### **Repeated assessments and attrition.**

Families will participate in 5 annual assessments. Wave 1, the baseline assessment will occur when youth are age 11 and approximately 3 months prior to implementation of SAAF. Wave 4 will occur just prior to the implementation of the SAAF–Teen. The final assessment, Wave 5, occurs approximately 10 months after implementation of SAAF—Teen. In previous

basic research and prevention trials

conducted at CFR, 5-year retention

rates ranged from 88% to 92% .

We plan conservatively for a 13%

attrition rate, ensuring that 400

[figure not shown]

participants (87% of 460) will complete the trial. Figure 5 presents the project timeline.

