**Alcohol and other drug use (Waves 1-5).**

The substance use assessment is designed to address the multidimensional nature of use. Items were selected from three well-validated measures for their sensitivity to intervention effects in our previous research at several levels of substance use. At the initiation level, group differences in the proportion of participants who transition from nonuse to use during the study can be detected. At the escalation level, group differences in the proportion of participants who increase their frequency/intensity of use during the study can be assessed. At the problem use level, group differences in specific substance-related behaviors and problems can be indexed. The basic items in the measure are those included in the Monitoring the Future study, which assess lifetime, annual, and 30-day prevalence and frequency of cigarette smoking, alcohol use, binge drinking, and marijuana use. For the purposes of the proposed study, a 3-month assessment will be added. A checklist of other drugs includes lifetime use of LSD/acid, Ecstasy, cocaine, heroin, other opiates, amphetamines, non-prescribed tranquilizers, and inhalants. Problems associated with substance use will be indexed using items from the Minnesota Student Survey for high school students and the Rutgers Alcohol Problems Index. These scales include items assessing dependence (e.g., had to use more to get same effect, tried to cut down but couldn't) and negative consequences of use (e.g., hurt relationships with friends or family, interfered with other activities, resulted in legal problems, missed school or work).

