#### **Aim 1.**

Mean differences in alcohol use by experimental group at wave 5 (~10 months after SAAF-T implementation) will be tested with structural equation models (SEM) as presented in Figure 6. These models are roughly equivalent to ANCOVA, but the SEM software permits FIML-based estimation of parameters as well as options for forming latent alcohol use constructs and greater precision in specifying and testing model parameters. We will investigate main effects on onset, frequency of use, binge use, and alcohol use problems as well as aggregate alcohol risk indices validated in prior trials to establish mean differences in use as a

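### Onset appears to be tested as any start of drinking by Wave 5, so drinking begun before SAAF-Teen costs power in the two contrasts that isolate that programme; an added time-specific onset model would recover much of it.

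*Combined protocol and SAP*

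**What the plan says.** Under Aim 1 the plan states: "Mean differences in alcohol use by experimental group at wave 5 (~10 months after SAAF-T implementation) will be tested". Onset is one of several outcomes: "We will investigate main effects on onset, frequency of use, binge use, and alcohol use problems", plus aggregate risk indices. On the model it says: "We will model outcomes with logistic (e.g., onset analyses), continuous, Poisson, or Negative Binomial distributions as appropriate". Within that sentence, the words "logistic (e.g., onset analyses" are all that ties onset to a model.

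The readable Aim 1 text does not say what counts as onset, from which wave, or among whom. The nearest description is in the measures section on alcohol and other drug use, which says that "group differences in the proportion of participants who transition from nonuse to use during the study can be detected". The same section has alcohol use, including lifetime use, assessed at all five waves, so the wave of first reported use will be known.

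On timing, the section on repeated assessments says: "Wave 4 will occur just prior to the implementation of the" SAAF-Teen programme. Wave 5 follows about 10 months after it. Under random assignment, the mid-adolescent and dual arms get SAAF-Teen at age 14, and families learn of that assignment only some months beforehand.

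**The concern.** Of the four follow-up intervals, three (Waves 1-2, 2-3 and 3-4) end before SAAF-Teen is delivered. A youth who first drinks in one of them has an onset that SAAF-Teen could not have prevented. If onset means any start by Wave 5, that youth still counts as an event in the mid-adolescent and dual arms, and similar youths count in the control and preadolescent arms. The shared early events narrow the relative difference and add noise.

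Two contrasts isolate SAAF-Teen: mid-adolescent versus control (neither had SAAF) and dual versus preadolescent (both had it). Both lose power. The trial exists to compare early, late and dual timing, so a null SAAF-Teen result on onset would be hard to read: the programme may do nothing, or the outcome may be carrying three years of earlier events.

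**Working it through.** **The plan's own power figure.** The Power section gives .80 for an effect of .13 and .90 for .15, with 100-115 families per group, and names no effect metric. Taking the effect as Cohen's f in a two-sided 1-df contrast on all 460 families, the noncentrality is N × f²: 460 × .13² = 7.77 and 460 × .15² = 10.35. Power is .795 and .894, so the figures reproduce. They do not reproduce for the 3-df four-group test on 460 (.636 and .773), or for the two-sided 1-df contrast on the 400 completers (.737 and .849). No power is stated for onset, so the loss has to be worked out separately.

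**Dilution.** Let p4 be the share who have started by Wave 4, and h0 and h1 the Wave 4-5 onset risks among remaining non-users without and with SAAF-Teen.

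- Risk of any start by Wave 5: p4 + (1 − p4) × h.
- Risk difference: (1 − p4) × (h0 − h1).

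The shrinkage by (1 − p4) is exact. Its size needs p4, which the documents do not give.

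**Assumed inputs:** h0 = .30, halved to h1 = .15; 100 completers per arm (400 completers over four arms); two-sided alpha .05; mid-adolescent versus control. For p4 = .20:

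- Control: .20 + .80 × .30 = .44. SAAF-Teen: .20 + .80 × .15 = .32. The difference is .12 instead of .15.
- Odds ratio for any start: (.32/.68)/(.44/.56) = .60. Among Wave 4 non-users: (.15/.85)/(.30/.70) = .41.
- Power is Φ[(difference − 1.96 × SE0)/SE1], with SE0 the pooled and SE1 the unpooled standard error. For any start, n = 100: SE0 = .0686, SE1 = .0681, giving .42. For Wave 4 non-users, n = 80: SE0 = .0660, SE1 = .0650, giving .62.

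| p4 | Risk difference, any start | Odds ratio, any start | Odds ratio, Wave 4 non-users | Power, any start | Power, Wave 4 non-users |
|---|---|---|---|---|---|
| 0 | .150 | .41 | .41 | .72 | .72 |
| .10 | .135 | .52 | .41 | .55 | .68 |
| .20 | .120 | .60 | .41 | .42 | .62 |
| .30 | .105 | .65 | .41 | .32 | .57 |
| .50 | .075 | .73 | .41 | .19 | .43 |

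With h0 = .20 halved and p4 = .20, the odds ratios are .69 and .44 and the powers .23 and .42.

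**Simulation with wave-by-wave onset and dropout.** Assumptions: 115 per arm, 13% attrition spread over the four intervals, and a SAAF-Teen hazard ratio of .5 in the Wave 4-5 interval. Started by Wave 4 is 1 minus the product of the first three interval survivals; for the first set, 1 − .97 × .95 × .93 = .14.

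| Assumed interval onset risks | Started by Wave 4 | Started by Wave 5 | Power, any start | Power, Wave 4 non-users |
|---|---|---|---|---|
| .03, .05, .07, .10 | .14 | .23 | .10 | .17 |
| .06, .09, .13, .18 | .26 | .39 | .15 | .29 |
| .10, .15, .20, .25 | .39 | .54 | .17 | .35 |

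With no SAAF-Teen effect, both tests rejected at or below about 5%, so the gain is not bought with false positives.

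**Why looking only at Wave 4 non-users is acceptable here.** Within each of the two pairs the arms had the same earlier treatment, so Wave 4 use is in effect a pre-treatment baseline. (Notice of SAAF-Teen may come shortly before Wave 4; any influence on earlier onset should be small.) Between arms that differ in SAAF at age 11, the same restriction would condition on something SAAF may have changed.

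**The case against.** The strongest reply is that cumulative onset is the right intent-to-treat outcome. Whole strategies are randomised, and drinking that starts before age 14 is a real consequence of intervening late. Aim 3 draws its effects, including initiation, from the Aim 1 analyses and needs that quantity. All of this stands. It is why the cumulative comparison should stay, and why a reader who infers that it is biased would be wrong: the .12 in the example is the true effect of the strategy on any start by Wave 5. The contrast is simply a weak test of SAAF-Teen itself.

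Second, the onset variable is inferred. The measures text describes what the instrument can detect, the model list is qualified as applying where appropriate, a person-period hazard model with a logit link is also logistic, and Figure 6 cannot be seen. This stands too. The concern holds on the most natural reading, and the lack of a stated risk set leaves the choice open until data are in hand.

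Two further inferences are tempting and not supported:

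- *That youth with a known onset who miss Wave 5 are discarded.* The plan commits to full-information maximum likelihood on all available data, both in the section on differential retention and under Aim 1. Even in a completers-only test, counting those known onsets changed simulated power by at most about .02.
- *That the plan ignores wave timing altogether.* Aim 1 says growth curves are to be considered, and the Power section addresses slopes. These concern use rather than onset, so they do not close this gap, but the repeated waves are not ignored.

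Finally, onset is one of several outcomes, and in the simulated scenarios the better analysis still reaches only .17 to .35. That limits what the change can deliver; it does not argue against it.

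**Conclusion.** The point holds in a limited form. If onset is any start of use by Wave 5, as the text most naturally reads, pre-programme onsets shrink the SAAF-Teen risk difference by (1 − p4) and reduce power in the two contrasts that isolate SAAF-Teen. The direction is arithmetic. The size depends on assumed onset rates and an assumed halving of Wave 4-5 onset: none at p4 = 0, .42 against .62 at p4 = .20 in the closed-form case, and .10 to .17 against .17 to .35 in the simulation. If SAAF lowers early onset, p4 and hence the dilution will be smaller for dual versus preadolescent than for mid-adolescent versus control. The whole-strategy comparison remains valid. The change is worth making because it is more powerful for a question central to the design and uses data already planned.

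**What to change.** Before analysis:

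1. Define onset and its risk set. Keep cumulative onset by Wave 5 among baseline non-users as the intent-to-treat comparison of the four arms and as the input to Aim 3.
2. Add a prespecified discrete-time onset model over Waves 2-5 among baseline non-users (logit or complementary log-log link, wave intercepts), with SAAF active from Wave 2 and SAAF-Teen active only in the Wave 4-5 interval.
3. Estimate the SAAF-Teen effect separately for mid-adolescent versus control and for dual versus preadolescent, by including a SAAF × SAAF-Teen interaction. Only these pairs are alike by randomisation up to Wave 4, and a single common term would assume that the later programme works equally with and without the earlier one.
4. State that contrasts mixing SAAF histories, such as mid-adolescent versus preadolescent or dual versus mid-adolescent, are read from the cumulative analysis.

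The cost is plan wording, one extra standard model and a sentence explaining hazard ratios. No new data are needed.

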### Power.

For experimental comparisons among four groups, a sample size of 100-115 families per group is sufficient to detect an effect of .13 with .80 power ( $\alpha < .05$ ) and a power of .90 for an effect as small as .15. For growth curve analyses ( $n > 100$  per group), we used algorithms to estimate the smallest intervention effect size we can detect with 80% power for changes in the slope parameter, assuming linear growth over four time points. With measurement reliability of 60%, we can achieve 80% power when the ES is 0.1 at posttest and ES is 0.2 at long-term follow-up. This suggests that we will have sufficient power to detect small to moderate intervention effects over time.

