| Screven                                                                                                   | 43     | 44            | 24.9                          | 47         |
| Warren                                                                                                    | 56     | 50            | 19.7                          | 56         |

Using data from the Department of Education , we estimated a pool of no less than 800 eligible households from which to sample 460 families (54.5%). Based on recruitment rates in our prior prevention trials (65%-90% of eligible household), an ample number of families will be available for us to reach our sampling goals.

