### Random assignment and contamination.

After pretest, families will be assigned randomly to one of four experimental groups: (a) *preadolescent inoculation*, (b) *mid-adolescent inoculation*, (c) *dual inoculation* control, and (d) control. Although the efficacy of SAAF and SAAF–Teen have been established, inclusion of a

control condition provides a baseline from which to compare normative alcohol use behavior in the population to both single- and dual-inoculation groups; it is also essential for comparing the single inoculations' economic efficiency. Preadolescent inoculation families will be assigned to receive SAAF at age 11 with no further intervention. Mid-adolescent inoculation families will receive SAAF–Teen at age 14. The dual-inoculation group will be assigned to receive both SAAF at age 11 and SAAF–Teen at age 14. The control condition involves no intervention contact. Participants will be notified if they are selected to participate in SAAF shortly after pretest. No participants will know if they are to receive SAAF–Teen until several months prior to its implementation. For each intervention implementation, families who are not attending a program receive written information by mail regarding adolescent development and alcohol use. Sending these materials is intended to maintain investment in the project for families who are not attending an intervention. No alcohol use effects are expected based on receiving written materials. All families will be followed across the course of the proposed study and assessed regardless of the number of intervention sessions they attend (intent-to-treat design). Information will be collected from family members about their participation in family enrichment programs offered in the school or community. The potential effects of participation in other programs (contamination) will be examined and statistically controlled in data analyses, as Lang et al. described.

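### The Aim 1 power figures (.80 for .13, .90 for .15) do not follow from the inputs given: an unadjusted four-group test reading the effect as Cohen's f has power .57-.64 and .71-.77

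*Combined protocol and SAP*

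**What the plan says.** The Power section introduces its first calculation with "For experimental comparisons among four groups". It states that "a sample size of 100-115 families per group is sufficient to detect an effect of .13 with .80 power" at alpha .05, "and a power of .90 for an effect as small as .15". It does not say whether .13 and .15 are Cohen's f, Cohen's d, a correlation or a standardized path. It also does not give the test, its degrees of freedom, a covariate R-squared or a multiplicity rule.

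The two ends of the range match figures elsewhere in the document. Enrolment is 460, or 115 per arm if allocation is equal. Under Repeated assessments and attrition, 400 "participants (87% of 460) will complete the trial", which is 100 per arm. Under Random assignment and contamination, "families will be assigned randomly to one of four experimental groups". Aim 1 tests "Mean differences in alcohol use by experimental group at wave 5" in structural equation models that the plan likens to ANCOVA.

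**The concern.** A power statement for a four-group comparison should be recoverable from the group size, the effect and alpha. The plain reading is Cohen's f in a 3-df test, and it gives clearly less than .80 and .90. If the stated figures came from a different test, a larger analysed N or an assumed covariate gain, the plan does not say so.

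The point matters most for dual inoculation against each single inoculation. Aim 3 sets dual inoculation against control and both single-inoculation arms, and it takes its effect estimates from Aim 1. A reader who assumes .80 power for those contrasts could take a null dual-versus-single result as evidence of no added benefit when the trial had limited ability to show one.

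**Working it through.** **Inputs from the documents.** Four groups; 100-115 per group (N = 400-460); effects .13 and .15; alpha .05.

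**Assumptions not in the documents.** Equal allocation; two-sided arm-versus-arm tests; effect read as Cohen's f unless stated; no multiplicity adjustment.

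**Formula.** Noncentral F with noncentrality λ = N·f²/(1 − R²), numerator df of 3 (four-group) or 1 (single contrast), and denominator df of N − 4 (one fewer with a covariate).

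**1. Which settings reproduce the plan's figures?**

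| Reading | λ for .13 / .15 | Power for .13 / .15 |
|---|---|---|
| Stated in the plan | not given | .80 / .90 |
| 1 df, N = 460, R² = 0 | 7.77 / 10.35 | .795 / .894 |
| 1 df, N = 400, R² = 0 | 6.76 / 9.00 | .737 / .849 |
| 3 df, N = 460, R² = 0 | 7.77 / 10.35 | .636 / .773 |
| 3 df, N = 400, R² = 0 | 6.76 / 9.00 | .568 / .707 |
| 3 df, N = 460, R² = .28 | 10.80 / 14.38 | .792 / .902 |
| 3 df, N = 400, R² = .38 | 10.90 / 14.52 | .796 / .904 |

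The unadjusted four-group test, which adds nothing to the stated inputs beyond the metric, misses by 16 to 23 points for .13 and 13 to 19 points for .15. Two kinds of setting reproduce both figures: a 1-df test on everyone enrolled, or a four-group ANCOVA with an R² that the plan does not state. A four-wave between-groups F at N = 400 with correlation .5 also gives .792/.902, but that is not the Wave 5 comparison described for Aim 1.

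**2. Sensitivity to R².** For f = .13 and R² from 0 to .5, four-group power runs from .57 to .88 at N = 400 and from .64 to .93 at N = 460.

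**3. Arm versus arm.** Noncentral t with n per arm and noncentrality d·√(n/2)/√(1 − R²). How a four-group f of .13 translates into d depends on the pattern of the four means:

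| Pattern | d | Power, n = 100 to 115, R² = 0 |
|---|---|---|
| Two arms high, two low | 2f = .26 | .45 to .50 |
| One arm apart from three equal arms | 4f/√3 = .30 | .56 to .62 |
| Two extreme arms, others midway: extreme pair | f√8 = .37 | .735 to .793 |
| Same pattern: extreme arm versus a midway arm | f√2 = .18 | .25 to .28 |

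With d = .26 and the R² that rescues the four-group test, power is .642 (n = 100, R² = .38) or .638 (n = 115, R² = .28). Reaching .80 at d = .26 needs R² of about .57 at n = 100 or .51 at n = 115.

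If .13 is itself Cohen's d, unadjusted arm-versus-arm power is .15 (n = 100) to .17 (n = 115).

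**4. Detectable effects at 100 completers per group, R² = 0.** Four-group test: f = .166 at .80 and .189 at .90. Arm versus arm: d = .40 (.398 before rounding) at .80 and .46 at .90.

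**The case against.** The best defence is that Aim 1 is ANCOVA-like, so covariate gain is part of the planned model. With R² of .28 at N = 460 (a correlation of √.28 = .53) or .38 at N = 400 (√.38 = .62), the stated figures hold for the four-group test. Even the 1-df test at N = 400 recovers to .799/.897 with R² of .14. Full maximum likelihood also uses partial data, so 400 complete cases may understate the information available. This defence stands to the extent that the figures could be right under an assumption the sponsor had in mind. It does not rescue the text, which gives no R² and needs a different one at each end of its own range.

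Three stronger readings are tempting and are not supported:

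- A reader might infer that the figures hold only for a single 1-df contrast on all 460 families. The ANCOVA settings reproduce them equally well. The ratio .15/.13 does not identify the degrees of freedom either: the detectable-effect ratio between .90 and .80 power is about 1.16 for 1 df and 1.14 for 3 df, and two-decimal rounding cannot separate them.
- A reader might infer that arm-versus-arm power is .45-.50 as a matter of fact. That rests on d = 2f with no covariate gain, the least favourable of the three four-arm patterns for the arms that differ most. With two extreme arms and the others midway, the extreme pair reaches .735-.793. If the extremes are dual and control, however, dual versus single drops to .25-.28.
- A reader might infer that the plan claims adequate power for small arm-versus-arm effects, or that it plans a 2×2 factorial analysis. It does neither. Its closing remark about small to moderate effects follows the growth-curve calculation, and the design is described as four groups.

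Figure 6, which shows the Aim 1 model, is not available in the text reviewed. It may define the contrasts.

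**Conclusion.** The concern holds in this form: the stated power is not delivered by the stated inputs. For an unadjusted four-group test with the effect read as f, power is .57-.64 rather than .80, and .71-.77 rather than .90. The stated values need either a 1-df test on all enrolled families, which falls to .737/.849 at 400 completers, or an unstated R² of about .28 to .38. Even with that R², arm-versus-arm power at d = .26 is about .64. These sizes depend on equal allocation, the f metric, alpha .05 without multiplicity adjustment and, for arm-versus-arm contrasts, the pattern of means. The documents do not settle the metric, the R² or the pattern, so the true power cannot be fixed at one number. The analysis itself is not shown to be wrong; the fault lies in the power statement.

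**What to change.** Replace the sentence in the Power section with detectable effects at 100 completing families per group, naming the metric, test and covariate assumption. Suggested wording: *With 100 completing families per group, two-sided alpha .05 and no allowance for covariate gain, power is .80 (.90) for Cohen's f = .166 (.189) in the four-group test and for d = .40 (.46) in each arm-versus-arm contrast.*

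If the sponsor relied on covariate adjustment, it should state and justify the R² and multiply these values by √(1 − R²). For example, R² = .38 gives f = .166 × .787 = .131 and d = .40 × .787 = .31 at .80 power. Arm-versus-arm power should still be reported, with dual versus each single inoculation shown explicitly.

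The cost is a wording change. Without a justified R², the stated detectable effect becomes less favourable. No extra families are needed.

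### The growth-curve power statement assumes one linear slope over four time points, but SAAF–Teen can act only between Waves 4 and 5 of five, so it does not cover the SAAF–Teen contrasts and its 80% cannot be verified

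*Combined protocol and SAP*

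**What the plan says.** Under Repeated assessments and attrition, "Families will participate in 5 annual assessments". "Wave 4 will occur just prior to the implementation of the" SAAF–Teen, and "The final assessment, Wave 5, occurs approximately 10 months after implementation of" it. Alcohol use is measured at every wave.

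Under Random assignment and contamination, the control and mid-adolescent arms receive no program before SAAF–Teen. The preadolescent and dual arms both receive SAAF at age 11 and differ only by SAAF–Teen at age 14.

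Under Aim 1, the first test is the difference in mean alcohol use at Wave 5. Latent growth models are then to be considered as well; they "permit evaluation of differences in the rates of change (including nonlinear trajectories) in alcohol use".

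Under Power, the growth-curve calculation seeks the smallest effect detectable "with 80% power for changes in the slope parameter", "assuming linear growth over four time points", with more than 100 families per group. At reliability 60% it reports that "we can achieve 80% power when the ES is 0.1 at posttest and ES is 0.2 at long-term follow-up". The section concludes that small to moderate effects over time can be detected. It does not say which four waves, which pair of arms, what scale the effect size is on, or what slope variance was used.

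**The concern.** The power statement describes an effect that starts at baseline and grows steadily. SAAF may act that way. SAAF–Teen cannot: Waves 1 to 4 all precede it and only one wave follows, so for SAAF–Teen posttest and long-term follow-up are the same wave. Two contrasts isolate SAAF–Teen: mid-adolescent versus control, and dual versus preadolescent. For both, a single slope either misses the effect or spreads a late change back over years in which the arms were treated alike.

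At stake is how the trajectory results are read. A null slope difference for SAAF–Teen could be taken as evidence of no effect, on the strength of a power claim that was not made for that contrast.

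**Working it through.** **Inputs from the documents.** Five annual waves; SAAF–Teen between Waves 4 and 5; 400 completers over four arms, 400/4 = 100 per arm; reliability 0.60; alpha 0.05.

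**Assumptions, because the documents are silent.** Two-sided test, both tails counted; normal approximation; continuous outcome; one pair of arms; baseline variance 1, split into 0.6 stable between-person and 0.4 error; random-slope variance s² from 0 to 0.05 per wave squared, uncorrelated with the intercept. Effects are in baseline SD units.

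**Step 1. The plan's 80%.** Code four points t = 0 to 3, so Σ(t − t̄)² = 5. With s² = 0 and baseline means free, the slope difference has variance 2 × 0.4/(100 × 5) = 0.0016, SE 0.040. With a common baseline mean, the generalised least squares (GLS) SE is 0.0357.

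| Reading of the effect size | Slope per wave | Power, baseline free | Power, common baseline |
|---|---|---|---|
| d = 0.2 at the last of four points | 0.2/3 = 0.067 | 0.385 | 0.464 |
| d = 0.1 per wave (0.1, 0.2, 0.3) | 0.100 | 0.705 | 0.800 |
| Cohen's f = 0.2, so d = 0.4 at the last point | 0.4/3 = 0.133 | 0.915 | 0.962 |

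These are best cases, since any slope variance lowers them. The third reading is plausible: the neighbouring effects of .13 and .15 reproduce as Cohen's f for a one-degree-of-freedom contrast at N = 460 (noncentrality 460 × 0.13² = 7.77 and 460 × 0.15² = 10.35; power 79.5% and 89.4%, against the stated .80 and .90). The plan's 80% is therefore neither reproduced nor refuted.

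**Step 2. What a straight line does to a Wave 5 effect E.** Over five waves the true difference is (0, 0, 0, 0, E), with t = 0 to 4, t̄ = 2 and Σ(t − t̄)² = 10.

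- Baseline free: slope = (4 − 2)E/10 = 0.2E, so the implied Wave 1-to-5 change is 4 × 0.2E = 0.80E. The intercept is E/5 − 2 × 0.2E = −0.2E.
- Common baseline (GLS, s² = 0): slope 0.181E, implied change 0.72E.
- Waves 1–4 only: every difference is zero, so the slope is 0.
- Waves 2–5 only: slope = 1.5E/5 = 0.3E, implied change over that span 0.90E.

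**Step 3. Power for that effect, 100 per arm.**

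- Five-wave slope, baseline free: variance 2(0.4/10 + s²)/100, so SE = 0.0283 at s² = 0 and 0.0424 at s² = 0.05. For E = 0.2 the slope is 0.04, giving z = 1.41 and 0.94.
- Wave 5 adjusted for Waves 1–4: at s² = 0 the residual variance is 1 − 4 × 0.6²/(0.4 + 4 × 0.6) = 0.486, so SE = √(2 × 0.486/100) = 0.0986 and z = 2.03 for E = 0.2. At s² = 0.05 the residual variance is 0.692, SE 0.118, z = 1.70.
- Wave 4-to-5 change: variance of the change 2 × 0.4 + s², SE 0.126 at s² = 0.

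| Test | E = 0.2 SD, s² = 0 to 0.05 | E = 0.4 SD, s² = 0 to 0.05 |
|---|---|---|
| Single slope, baseline free | 0.293 to 0.156 | 0.807 to 0.470 |
| Single slope, common baseline | 0.296 to 0.145 | 0.812 to 0.430 |
| Wave 4-to-5 change | 0.353 to 0.335 | 0.885 to 0.866 |
| Wave 5 adjusted for Waves 1–4 | 0.528 to 0.398 | 0.982 to 0.925 |

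The last row is the relevant comparator. If two arms share the same mean path through Wave 4, the GLS estimate of their Wave 5 difference is the Wave 5 difference adjusted for Waves 1–4.

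**The case against.** The strongest reply is that linear growth over four points is a simplification made only for the power calculation. The Aim 1 text allows nonlinear trajectories, and a piecewise curve is one. The growth models are an additional look. The first Aim 1 test is the Wave 5 mean difference, Aim 2 targets Wave 5 use, and Aim 3 takes its effects from the Aim 1 analyses. All of this stands, and it limits the point to the trajectory analysis. It does not remove it: permission to fit a nonlinear curve names no change point, and the only growth parameter given a power figure is a linear slope.

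A reader might infer three stronger things that the documents do not support.

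- That the stated 80% is false. It fails if the effect size is a standardized mean difference of 0.2 at the last of four points for one pair of arms, but Step 1 shows readings that reach it. Where it fails, it does so under perfectly linear growth, so the wave mismatch is not the cause.
- That the trial is biased against SAAF–Teen or cannot settle dual versus single. The Wave 5 comparison captures SAAF–Teen without dilution.
- That 40% of the effect is lost. That figure is the fitted Wave 5 level (−0.2E + 0.8E = 0.6E), which includes a spurious baseline difference. The slope test itself loses 20–28%.

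**Conclusion.** The point holds for the growth analysis and for the two contrasts that isolate SAAF–Teen. The power assumption does not fit a five-wave design with one wave after SAAF–Teen. A single slope carries none of the effect over Waves 1–4 and about 0.72 to 0.80 of it over Waves 1–5, and its power is clearly below that of a test aligned with the design whether the effect is 0.2 or 0.4 SD. The dilution depends only on an effect confined to Wave 5 and a straight-line fit. The power figures depend also on the assumed slope variance and the other assumptions listed in the working. The 80% is best described as unverifiable. This is a worthwhile, inexpensive correction to a supporting analysis; it does not threaten the main Aim 1 comparison.

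**What to change.** For the trajectory analysis, specify a piecewise growth model with a knot at Wave 4. SAAF assignment acts on the Wave 1–4 segment. SAAF–Teen assignment and its interaction with SAAF act on the Wave 4-to-5 change. Arms treated alike through Wave 4 share a common Wave 1–4 trajectory (control with mid-adolescent; preadolescent with dual). That constraint supplies much of the gain: the unconstrained change contrast reaches only 34–35% at 0.2 SD, against 40–53%. Because families learn of SAAF–Teen several months beforehand, possibly before Wave 4, report a check of the constraint.

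Replace the growth-curve power sentence with five-wave figures for this model, stating the effect-size metric, the contrast and the slope variance. Give the interaction its own figure: it is a difference between two pairwise contrasts, so with equal arms its variance is about double. Do not substitute a detectable effect of 0.30–0.34 SD, which is what Step 1 implies at 80% power (2.80 × 3 × 0.0357 = 0.30 and 2.80 × 3 × 0.040 = 0.34), because that is a four-point figure with zero slope variance.

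The cost is SAP wording and one rerun of the power calculation, with no change to data collection. The stated detectable effect may become less favourable.
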